### Equivalence of clinical vignettes

We will develop two comparable lots of clinical vignettes focusing on different medical topics. In order to preserve comparability we will select vignettes with similar, optimal psychometric characteristics [21-23]. They will be ranked for the following psychometric properties: validity of users' judgement, content validity, internal consistency, and responsiveness.

To avoid contamination, we will make sure that the vignettes in lots A and B are different so that learning about the management of lot A conditions does not influence management of lot B conditions. For example, there may be contamination if lot A focuses on ischemic heart disease (and highlights the need to optimize diabetes control in diabetics) and lot B focuses on diabetes (and highlights the need to optimize control of ischemic heart disease risk factors).

The authors will analyse the cumulative profile of the psychometric characteristics of each vignette and will select valid, reliable, and distinct vignettes. These will then be balanced to the intervention arms to have two comparable lots, avoiding contamination. The flow of vignette selection through the different phases is presented in Figure 5. We cannot estimate how many vignettes will reach the threshold for validity and reliability to be considered appropriate. We will stop selection only when we have at least six appropriate vignettes for the two ECCE arms in the incomplete block design.

**Figure 5 F5:**
[figure not shown]
The flow of vignette selection through the different phases.

### Study participants

This study will involve Italian doctors naïve to ECCE who voluntarily agree to participate. Doctors can learn about this research program through advertisements in medical journals and websites. New users who enter the ECCE website will be automatically invited to participate. There will be no exclusion criteria.

### Allocation to experimental arms

The Italian Cochrane Centre will produce the computer algorithm for the allocation sequence and will implement it on ECCE. Once doctors agree to participate, ECCE will assign doctors to one of the three arms using a balanced randomisation scheme. Researchers will be unable to manipulate the randomisation sequence or interfere with the ECCE registration process. In Figure 6, we present a flow chart outlining the progress of participants through the study. This protocol follows the recommendations of the Consort Statement [Additional file 1] [24].

**Figure 6 F6:**
[figure not shown]
The flow of participants through the different trial steps.

### Intervention

Doctors randomised to ECCE will have access to their clinical vignettes for three months after enrolment, or until they finish all vignettes. All participants will have a logbook to indicate how many times they accessed the platform and how much time they spent solving clinical vignettes. Doctors randomised to receive a printed copy of *Clinical Evidence *may use it as much as they want over the whole trial period and may have access to the on-line version of *Clinical Evidence*. The ECCE platform will always be inaccessible to them during the intervention period. After the intervention period, a sample of contamination-controlled clinical vignettes will be accessible to arm 1 and 2 participants until the end of the trial.

### Outcomes measures and measurements

The primary outcome will be basic knowledge of the *Clinical Evidence *contents assessed through the scores from the clinical vignettes. The test will consist of fixed and multiple-choice questions from the selected valid, reliable vignettes and will be administered before (pre-test), immediately after (approximately 16 weeks after enrolment, post-test one), and six months after the intervention (approximately 36 weeks after enrolment, post-test two) (see Figure 6).

To reduce the risk of a test-training effect (practice effects or memory of the first administration will influence post-test performance) at each test section ('pre-test', 'post-test one' and 'post-test two'), we will randomly select two vignettes from lot A and two from lot B to avoid repetition. Therefor, each participant will have only a limited probability (approximately zero) of test/re-testing the same vignette from one assessment to another. The questionnaire will investigate the same *Clinical Evidence *knowledge for intervention and control chapters. This random sampling of outcomes with high psychometric standards will eliminate any interactions between the causal relationship and the classes of outcomes studied or not studied within the same group of vignettes [25]. To prevent participants from guessing which vignettes will be evaluated, we will add a number of "distracter" vignettes to lots A and B. All groups will also rate their satisfaction with the information source and its perceived value for their medical education and clinical practice.

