**Design:**

All Italian doctors naïve to ECCE will be randomised to three groups. Group one will have access to ECCE for *Clinical Evidence *chapters and vignettes lot A and will provide control data for *Clinical Evidence *chapters and vignettes lot B; group two vice versa; group three will receive the concise printed version of *Clinical Evidence*. There are in fact two designs: a before and after pragmatic trial utilising a two by two incomplete block design (group one versus group two) and a classical design (group one and two versus group three). The primary outcome will be the retention of *Clinical Evidence *contents assessed from the scores for clinical vignettes selected from ECCE at least six months after the intervention. To avoid test-retest effects, we will randomly select vignettes out of lot A and lot B, avoiding repetitions. In order to preserve the comparability of lots, we will select vignettes with similar, optimal psychometric characteristics.

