### Aim of the study

This trial will test the effectiveness of ECCE e-learning program for transferring EB information to medical doctors after a median of three months of ECCE usage, and retention of the information after a median period of six months. The main hypotheses to be tested are: 1) Does an e-learning CME program based on *Clinical Evidence *and clinical vignettes (ECCE) increase physicians' basic knowledge about epidemiology, therapy, prognosis, and risk factors in a clinical scenario? 2) Do physicians retain the knowledge from the ECCE for more than six months? 3) Is this educational intervention superior to the passive diffusion of information through the printed version of *Clinical Evidence*?

The secondary hypotheses are: Does ECCE modify physicians' attitudes to EB behaviours in a simulated realistic clinical scenario?

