### Sample size and calculation of power

Based on a preliminary examination of test scores, we established that the smallest useful difference for this intervention was a 20% absolute improvement. Based on a preliminary test of 300 doctors, we found that a 28% absolute improvement was due to the intervention. We standardised the absolute improvement across different type of vignettes (five or ten questions). Therefore we calculated our sample size to detect a 0.7 standardized difference in the primary outcome, set the α error rate at 0.05 (two-sided), and the β error at 0.10 (90% power). This yielded a sample size of 45 practitioners per study arm. If the accrual period is six months, and the maximum follow-up period is six months with a loss during follow-up of 20% at the end of the study, the total number of practitioners to be randomised has been adjusted upwards to 162 (54 per intervention group).

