### Statistical analyses

Knowledge test data will be analysed using repeated-measure analyses of variance (ANOVA), reporting the partial omega squared (ù2) effect size with corresponding 95% confidence interval. Scores for the    knowledge test scale will be subjected totwo-by-three [TO TWO-BY-THREE] repeated-measures ANOVA having: 1) one between-subjects factor (ECCE lot A and ECCE lot B) and one within-subject factor (pre-test, post-test one and post-test two) for the incomplete block design trial; 2) one between-subjects factor (ECCE set and control) and one within-subject factor (pre-test, post-test one and post-test two) for the classical trial. Tests of Sidak-adjusted simple main effects will be used for post-hoc mean comparisons as needed. Orthogonal planned contrasts will be formulated for the knowledge test data to verify knowledge retention. We do not expect the data sets to follow normal distributions and assumptions completely. If this is the case, we will do nonparametric and robust analyses to explore differences in medians or distributional shapes. If nonparametric analysis yields similar interpretations and conclusions, we will focus on the parametric results.

Additional analyses will include examination of the relationship between knowledge test outcomes and potential moderator variables including sex, age, and years of practice, speciality (*e.g*., general internal medicine versus general surgery); preferred CME format; computer skills; ease using the internet; familiarity with and readiness to use EB information; study drop-out; satisfaction with learning experience, and frequency of attending residential and distant CME activities. For these analyses, we will use parametric methods (regression, repeated-measures ANOVA, analyses of covariance (ANCOVA)) and nonparametric methods (Wilcoxon-Mann-Whitney test, χ^2 ^test of independence and γ measure of association) as needed, based on the data. Holm's modified Bonferroni corrections will be applied to check experimental error (*e.g*., in exploratory analyses). Analyses will be done based on an intention-to-treat basis, whether or not doctors logged and took credits. We will restrict the explanatory analysis to those doctors who took credits. All the analyses will consider *p *= 0.05 as significant (two-sided).

SAS version 9.0 statistical software (SAS Institute, Inc, Cary NC) will be used.

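### The primary outcome is defined inconsistently (late retention in the Abstract, knowledge over three sessions in Methods), so the stated alpha and power belong to no identified test

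*Protocol article*

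**What the plan says.** - **Abstract, Design:** "The primary outcome will be the retention of" what the compendium teaches. The same sentence also sets the time, since this outcome is to be "assessed from the scores for clinical vignettes selected from ECCE at least six months after the intervention". This is one concept at one late time.
- **Outcomes measures and measurements:** "The primary outcome will be basic knowledge of the" Clinical Evidence contents, from vignette scores. The test "will be administered before (pre-test), immediately after (approximately 16 weeks after enrolment, post-test one") and again at about 36 weeks (post-test two). No session is called primary.
- **Aim of the study:** "The main hypotheses to be tested are" three, numbered but not ranked: knowledge gain, retention beyond six months, and superiority to print.
- **Sample size and calculation of power:** the trial is sized "to detect a 0.7 standardized difference in the primary outcome", at two-sided 0.05 and 90% power, giving 45 per arm. No comparison, lot or session is named.
- **Statistical analyses:** there is one two-by-three repeated-measures ANOVA for the block design and one for the classical design, plus planned contrasts for retention. Sidak adjustment is for post-hoc mean comparisons. "Holm's modified Bonferroni corrections will be applied to check experimental error", with exploratory analyses given as an example. The 0.05 level then applies to every analysis.

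**The concern.** Two sentences in one document each define the primary outcome, and they can give opposite results. Suppose ECCE raises scores at post-test one but the effect has gone by post-test two. Under the Abstract the primary result is negative. Under Methods, the post-test one result is part of the primary outcome and can be reported as success. Because the Aim counts gain and retention as separate hypotheses, the authors themselves treat these as different questions.

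The sample size section does not settle the matter, since it refers only to the primary outcome. The multiplicity statements do not settle it either, because neither Sidak nor Holm is tied to the three main hypotheses. If the definition is chosen after the scores are known, the 5% level no longer describes the headline claim. The article also says that the researchers are not blinded to allocation.

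**Working it through.** **1. The plan's own figure.** Inputs from the sample size section: d = 0.7, two-sided alpha 0.05, power 0.90.

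n per arm = 2(z₀.₉₇₅ + z₀.₉₀)² / d² = 2(1.960 + 1.282)² / 0.49 = 42.9, so 43. The t-test version gives 43.9, so 44. The stated 45 gives power 0.907 (t-test). It therefore reproduces, within one or two doctors, as a single two-arm comparison of a single score at an unadjusted 0.05.

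**2. Which test does it belong to?** The two definitions side by side:

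| | Abstract | Methods |
|---|---|---|
| Concept | retention | basic knowledge |
| Time | at least six months after the intervention | three sessions, none primary |
| Post-test one positive, post-test two negative | primary result negative | positive claim possible |

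**3. Size if any success counts.** For k independent tests at 0.05, the chance of at least one false positive is 1 − 0.95^k. With k = 2 this is 0.0975, and with k = 3 it is 0.143.

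The real tests are correlated, so I simulated them under the null (600,000 runs per cell, normal scores, equal arms). The block contrast is trained lot minus untrained lot over arms I and II. The classical contrast is the trained-lot mean of arms I and II minus the print-arm mean over both lots, at post-test two. The article gives no correlations; the ranges are assumptions.

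| Between-session correlation | Block contrast at either post-test | Plus ECCE versus print at post-test two |
|---|---|---|
| 0.3 | 9.4-9.5% | 13.6-13.9% |
| 0.5 | 9.1% | 13.1-13.5% |
| 0.7 | 8.3-8.4% | 12.5-12.8% |

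Within each row, the range covers between-lot correlations of 0.2, 0.5 and 0.8.

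**4. If the main tests shared 0.05 instead.** By Bonferroni (t-test), two tests need 52 per arm and three need 57. With 45 per arm, power per test is 0.85 for two and 0.81 for three. So reading Holm as covering the main hypotheses would leave the stated 90% power unsupported at Holm's first step.

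**5. Does the power carry over to the block contrast?** Let σ be the SD of a one-lot score and ρ the between-lot correlation. Arm I versus arm II on one lot has variance 2σ²/n. The trained-minus-untrained contrast is half the arm difference in each doctor's lot difference. Its variance is (1/4) × 2 × 2σ²(1 − ρ)/n = σ²(1 − ρ)/n. The ratio is (1 − ρ)/2, which is 0.40, 0.25 and 0.10 for ρ = 0.2, 0.5 and 0.8. Precision thus depends strongly on a quantity that the article does not state, and the article does not say which SD the 0.7 refers to.

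**The case against.** **The two statements can be read together.** Methods may give the construct and the schedule, and the Abstract the time. Methods name no rival primary time, and the sample size section speaks of six months' follow-up and loss at the end of the study. Post-test two is then the likeliest primary session. This stands as a sensible guess at intent, and it is why the fix adopts that session. It does not remove the inconsistency, because the Aim separates gain from retention.

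**Multiplicity is not ignored.** A reader might infer that Holm is confined to exploratory work. The text does not say so: exploratory analyses are only an example. What stands is that Holm's scope is unclear and that the main hypotheses are not named under it.

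**Separate questions may each be tested at 0.05.** The study design section gives the two designs different questions, and reporting each on its own is defensible. The inflation above applies only if success on any one of them would be claimed as the trial's success.

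**Larger error rates.** A reader might count the four rows of Table 1 as separate unadjusted tests and arrive at about 16% at one post-test, or 26-29% at both. The documents do not support this. The Abstract pools groups one and two against group three, the analysis section plans one ANOVA per design, and each Table 1 row requires a rise in one score together with no change in another, which is not a single 5% test.

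**The sample size.** A reader might also infer that 45 per arm is miscalculated for its stated inputs. It is not; only the test that it supports is missing.

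**Conclusion.** The concern holds as an internal inconsistency that should be fixed. The primary outcome has two definitions that can lead to opposite conclusions, and the stated alpha and power are attached to no named comparison or session. The possible inflation is moderate: about 8-10% for the block contrast at either post-test, and about 12-14% with ECCE versus print added, against a stated 5%. These figures assume between-session correlations of 0.3-0.7, between-lot correlations of 0.2-0.8, and a claim of success on any one test. The inconsistency itself rests on no assumption. How far to control error across distinct questions, and in what order, is partly judgement.

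**What to change.** - In the Abstract, Outcomes and Sample size sections, state one primary session and comparison: post-test two in the block design, arm I versus arm II, at two-sided 0.05. Post-test two is the assessment that the Abstract's time already points to.
- State that the sample size refers to that test. If the trained-minus-untrained contrast is used, restate the 0.7 SD and the power with an assumed between-lot correlation and its range.
- Label post-test one and ECCE versus print as key secondary, either in a pre-stated order or under Holm. The order is the sponsor's choice. Say plainly what Holm covers.
- Base the retention claim on the post-test two contrast and its confidence interval. A non-significant fall from post-test one to post-test two does not show retention.

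The cost is small: no added participants, sessions or data, and one short power calculation if the within-doctor contrast is chosen. The downside is that the other main hypotheses become secondary or conditional.

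### For doctors who use the full three months of ECCE access, post-test two at about week 36 comes about 5.3 calendar months after access ends, short of the six months that the primary outcome and hypothesis 2 require

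*Protocol article*

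**What the plan says.** All references are to the Protocol article.

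- **Intervention:** doctors in the ECCE arms "will have access to their clinical vignettes for three months after enrolment, or until they finish all vignettes".
- **Outcomes measures and measurements:** the last test is given "six months after the intervention (approximately 36 weeks after enrolment, post-test two". Study procedures and data collection repeats weeks 16 and 36 as the e-mail follow-up times for participants.
- **Abstract, Design:** the primary outcome is retention, scored "at least six months after the intervention".
- **Aim of the study:** hypothesis 2 asks: "Do physicians retain the knowledge from the ECCE for more than six months". The opening sentence of the same section describes the retention period differently, as a median of six months following a median of three months' use.

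The Outcomes section defines the primary outcome as knowledge scored from the vignettes at three tests and does not single out the last one. The Abstract does single out the late measurement, and post-test two is the only scheduled test that could meet it.

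**The concern.** The article treats week 36 from enrolment as six months after the intervention. Once the three months of access are taken off, week 36 leaves less than six calendar months. The Abstract makes six months a minimum, and hypothesis 2 asks about something longer, so a nominal date below six months matters for both statements.

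At stake is one of the three main hypotheses. If the test is run as scheduled, a statement that knowledge lasted beyond six months would not be supported for doctors who used their full access, whatever the scores show.

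**Working it through.** **Inputs**

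- Longest access: 3 months from enrolment (Intervention).
- Post-test two: about week 36 from enrolment (Outcomes measures and measurements; Study procedures and data collection).
- Required interval: at least 6 months (Abstract, Design) and more than 6 months (Aim of the study, hypothesis 2).
- Length of a month. The article does not define it, so three conventions are shown. A calendar month is 365.25 / 12 / 7 = 4.348 weeks.

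**Step 1. Can the article's equivalence be reproduced?** With four-week months it can: 3 × 4 + 6 × 4 = 12 + 24 = 36 weeks. This may be how week 36 was obtained. With calendar months it cannot: 9 × 4.348 = 39.1 weeks.

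**Step 2. Interval for a doctor using full access**

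Interval in months = (36 − 3 × w) / w, where w is the number of weeks in a month.

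| Convention | w | End of access (week) | Gap to week 36 (weeks) | Gap (months) | Week at which 6 months is reached |
|---|---|---|---|---|---|
| Calendar month | 4.348 | 13.04 | 22.96 | 5.28 | 39.1 |
| 30-day month | 4.286 | 12.86 | 23.14 | 5.40 | 38.6 |
| Four-week month | 4.000 | 12.00 | 24.00 | 6.00 | 36.0 |

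In calendar months the shortfall is 39.13 − 36 = 3.1 weeks, or 6 − 5.28 = 0.72 month (12% of six months).

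**Step 3. Who does reach six calendar months at week 36?** The latest qualifying end of access is 36 − 6 × 4.348 = 36 − 26.09 = week 9.9. Doctors who complete all their vignettes by about week 10 qualify, and later finishers do not.

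**Step 4. Does the most favourable convention rescue both statements?** Four-week months give exactly 6.0. That meets a minimum of six months by equality. It does not meet hypothesis 2, which asks about more than six.

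**Step 5. Would week 40 be enough?** 40 − 13.04 = 26.96 weeks, and 26.96 / 4.348 = 6.2 calendar months. This satisfies both statements even for a doctor who uses all of the access time.

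**The case against.** The strongest defence is that the date is only approximate and the gap is small. Week 36 is given as approximate and matches nine four-week months. The e-mail goes out at week 36, so tests answered after it will be somewhat later. Some doctors finish early, and the Aim section also speaks of a median of six months. All of this is fair and keeps the point modest. It does not remove it. A late reply lengthens the interval by chance and not by design. The median wording does not help clearly either: if the median of three months' use means time until access ends, at least half the doctors run to the three-month cap, and the median interval at week 36 is then about 5.3 months.

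A reader might infer several stronger things that the article does not support:

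- **That the late endpoint is not measured.** It is. Post-test two is scheduled and scored, nominally about 0.7 month early for full-access doctors.
- **That the gap is only 4.6 months.** This counts the 20 weeks from post-test one, described as "immediately after (approximately 16 weeks after enrolment, post-test one". But the six months are stated as running from the intervention, which ends at three months or on completion.
- **That the sample-size section contradicts the schedule.** Its statement that "the maximum follow-up period is six months" can be read as time after the intervention, which agrees with the Outcomes section.
- **That the 20% loss allowance covers too short a period.** The article attaches it to the end of the study, whichever week that is.
- **That the shorter interval favours ECCE.** No rate of forgetting is given, so no size can be put on three weeks. All arms are tested at the same weeks, so timing does not bias the comparison between them.

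**Conclusion.** The point stands as a timing inconsistency of minor to moderate importance. For a doctor who uses the full three months, the nominal interval from end of access to post-test two is 23.0 weeks, or 5.3 calendar months. That is about 3 weeks below the Abstract's minimum and below what hypothesis 2 asks. No month convention examined gives such a doctor more than six months at week 36.

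This rests on two assumptions: that the intervention ends when the three-month access ends, as the Intervention section implies, and that the test is taken at its nominal week. The schedule does not bias the comparison between arms, and the sample-size calculation does not depend on whether the test falls at week 36 or week 39. The consequence is confined to the retention interval that the trial can report, and so to how hypothesis 2 can be answered.

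**What to change.** State once that the retention interval runs from the end of ECCE access. Because a sample of vignettes stays open to arms 1 and 2 until the trial closes, say that this means the end of the three-month access period, or earlier completion. Then choose one of two courses:

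1. **Move the test.** Send the second test e-mail at week 40 or later, to all arms alike. The Abstract's minimum and hypothesis 2 can then stand as worded. The cost is a new date for an automated e-mail and about 4 weeks more follow-up.
2. **Keep week 36 and change the wording.** In the Abstract, in the Aim of the study (hypothesis 2 and the median statement) and in Outcomes measures and measurements, describe the interval as about five months after the end of access. This costs only wording, but the trial then gives up the claim of retention beyond six months.

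Under either course, use one description of the interval in place of the present mix of minimum, median and approximate six months.
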